## Results

Project evaluation will proceed using the Reach, Effectiveness, Adoption, Implementation, and Maintenance (RE-AIM) Framework [34] and the Alberta Quality Matrix for Health [35]. Specifically, dimensions considered will include the following: acceptability (subscriber satisfaction/experience), accessibility (ease of subscription to and utilization of the Text4Hope program), appropriateness (numbers of residents subscribing to the program), and effectiveness (6- and 12-week changes in the Perceived Stress, GAD-7, and PHQ-9 scales). It may also be possible to examine efficiency (cost avoidance and efficiencies through reduced need for face-to-face counselling) and safety (self-reports of decreased crisis and urgent service calls, and decreased emergency medical services utilization rates).

We will evaluate the efficacy of Text4Hope with the reductions of perceived stress, anxiety, and depression at 6 weeks and 12 weeks. Data analysis will include the standard use of parametric and nonparametric techniques (eg, within-subject general linear models), including multiple comparison Type 1 error corrections. Power analysis with effect sizes based on [name] group research publications [26-28,36,37] indicates a sufficient effect size for the expected Text4Hope program subscriber sample size. As the sample size for the data set generated from this project will be large, in addition to the conventional statistics used in these projects, we plan to adopt a “big data” analysis approach to examine data-driven patterns. Using machine learning and data mining methods, we expect to capture the most powerful window on differences and high-order sets of potential interactions. With our program targeting 300,000 Canadians to self-subscribe, with an expected 60,000 completing the survey, we are confident that this project has adequate power for our basic cross-sectional approach. We will develop predictive models using baseline measurements (features) and machine learning algorithms (eg, the least absolute shrinkage and selection operator [LASSO], support vector regression [SVR], and random forest regression, etc [38-40]) to predict the efficacy of our intervention at 6 and 12 weeks, as measured by the change in assessment scores (eg, GAD-7, PHQ-9) compared to the baseline. We will perform a 10-fold cross-validation to evaluate the performance of the models. During cross-validation, the data will be randomly segmented into 10 folds, with each fold containing 10% of the data. For each iteration, 1 fold will be left out as the testing data and the remaining 9 will be the training data. Within each training session, another internal 10-fold cross-validation will be used to select the best features, algorithm, and corresponding hyperparameters as the model to be trained on this specific training session. The selected model in the training data will then be applied to the testing data. This procedure is crucial for predictive tools as the data being tested has never been seen in any way by the model. The performance of the models will be evaluated using the Pearson correlation between the predicted and actual reduction of the outcome measures.

Due to the ongoing shifts in infection rates and public health measures over time, together with a shifting and unpredictable pattern of economic impacts, it will be important to include data on infection and death rates as well as the overall economic measures (including unemployment rates) associated with the baseline, 6-week, and 12-week measures. Such variables will be included in the machine learning analysis of the project data [41]. Including these variables will enable the model to account for variables that may influence expected rates of anxiety- and depression-related symptoms.

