Supportive text messages are associated with positive outcomes, including the reduction of depressive symptoms, increased abstinence duration in alcohol use disorder, and high user satisfaction, as reported in previous research. For example, in randomized controlled trials (RCT), patients with depression that received supportive text messages showed symptom reduction on a standardized self-report when compared to a similar patient group that did not receive text messages (with large effect sizes: Cohen *d*=0.85, Cohen *d*=0.67) [26,27]. In another RCT, to evaluate the effectiveness of an addiction-related supportive SMS text messaging mobile intervention in improving treatment outcomes for patients with alcohol use disorder, small to moderate effects were found for the cumulative abstinence duration. In addition, the intervention group's mean time to first day to drink was over twice the length of that of the control group (60 versus 26 days, respectively) [27]. In two user satisfaction surveys, over 80% of subscribers reported that a supportive SMS text messaging program improved their mental health [27,28]. Subscribers reported text messages made them feel more hopeful about managing issues (82%), in charge of managing depression and anxiety (77%,), and connected to a support system (75%); in addition, such messages improved their overall mental wellbeing (83%) [27].

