### Outcome Measures

The primary outcome is changed scores at 6 and 12 weeks from baseline on the Perceived Stress, GAD-7, and PHQ-9 scales. The secondary outcomes are the following: (1) changes in prevalence rates for perceived stress, anxiety, and depression from the early phase of the COVID-19 pandemic to a later phase, as measured with the Perceived Stress, GAD-7, and PHQ-9 scales, respectively; (2) the interaction between primary outcomes and the demographic characteristics of subscribers as well as the date of subscription to Text4Hope relative to the phase of the pandemic in Alberta; and (3) subscriber satisfaction/experience.

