### Hypotheses

Our hypotheses, based on previous research, are as follows: (1) High rates of stress, anxiety, and depression will be reported, affecting one-third to half of the general population; the 1-week prevalence rates for these disorders will increase as the pandemic continues, compared to rates in the early phase. (2) Specific risk factors will be found for the experience of distress during the pandemic, such as female gender, risk of exposure, and social determinants of health (eg, employment, housing). (3) The intervention will result in a 25% or greater reduction in perceived stress, anxiety, and depressive symptoms (as measured by the Perceived Stress, GAD-7, and PHQ-9 scales) at 6 and 12 weeks from baseline. (4) At least 80% of subscribers will express satisfaction with the Text4Hope program and perceive the daily supportive text messages as contributing to their overall mental well-being.

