Limitations of this protocol include a lack of baseline data on stress, anxiety, and depression levels before self-isolation measures were implemented in Alberta; this was unavoidable as our study was initiated shortly after quarantine and self-isolation measures were introduced. Nonresponse bias may also affect the expected results, as program subscribers are a sample of the population, not the entire population of the province. Nonrespondents may differ in a systematic way compared to respondents. For example, they may differ in their baseline level of mental wellness, be more (or less) affected by the pandemic, or have limitations in literacy or English fluency. In view of the limitations noted above, any prevalence estimates must be interpreted with caution, and compared to the conventional baseline of subsequent conventional prevalence estimates. The authors also note that this protocol does not include a control group and this raises the question of specificity concerning hypothesis 3, which concerns reductions in perceived stress, anxiety, and depressive symptoms. Previous RCT work from this group has demonstrated the efficacy of supportive SMS text messaging in intervention groups, compared to control groups that did not receive supportive text messages; instead, the control group received the same survey requests as the intervention group in addition to a single text message every 2 weeks, thanking them for participating in the study [26,37]. Given the intention to provide support to the catchment population of this study and the prior evidence for efficacy, it would be unethical to include a control group in the current protocol. Nevertheless, prior studies did include subscriber satisfaction surveys, as does this protocol, and that measure will provide evidence for engagement of the subscribers with the program (simply put, if subscribers ignored the text messages, it is highly unlikely that there would be positive satisfaction survey results). In the current health implementation context of this protocol, the comparison of changes in outcome measures in relation to comparison with effect sizes from our prior work (together with an assessment of the degree of correspondence of subscriber satisfaction survey responses to changes in our outcome measures) will be a good indicator of subscriber engagement in the absence of a control condition. Despite these limitations and possible bias factors, our protocol will provide useful data about the mental health characteristics of individuals in the early stages of the COVID-19 pandemic. We expect that our results will represent an important initial source of information for government and health care planners in determining the nature and quality of services required to address mental health challenges arising during this pandemic, as well as future pandemics that employ self-isolation or quarantine measures. Specifically, planning for and implementing virtual care programs, including supportive SMS text messages, may be a fruitful approach to supporting isolated or quarantined individuals. In addition, we expect the supportive SMS text messaging intervention to have a positive effect on mental well-being and we will be able to measure this well within the expected sample size.

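### Hypothesis 3 and the efficacy criterion credit Text4Hope with an uncontrolled change from baseline, so background drift or regression to the mean could be read as efficacy or could mask it

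*Protocol article*

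**What the plan says.** Under Outcome Measures: "The primary outcome is changed scores at 6 and 12 weeks from baseline on the Perceived Stress, GAD-7, and PHQ-9 scales". Under Hypotheses, the third reads "The intervention will result in a 25% or greater reduction in perceived stress, anxiety, and depressive symptoms", at 6 and 12 weeks. Under Results: "We will evaluate the efficacy of Text4Hope with the reductions of perceived stress, anxiety, and depression at 6 weeks and 12 weeks", with "within-subject general linear models" given as an example of the technique and a correction for multiple comparisons.

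The Results section also recognises that infection rates, public health measures and the economy will shift during follow-up. It assigns the corresponding data to one place: "Such variables will be included in the machine learning analysis of the project data". Those models predict each person's change and are scored by the correlation of predicted with actual change. Subscription date relative to the phase of the pandemic appears under Outcome Measures as part of a secondary interaction.

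The Discussion states that there is no control group, that this leaves the specificity of hypothesis 3 open, and that a control would be unethical. It then names two comparisons. One is "the comparison of changes in outcome measures in relation to comparison with effect sizes from our prior work"; the other is how far satisfaction responses track outcome change. Together, it says, these "will be a good indicator of subscriber engagement in the absence of a control condition". The Discussion also says that scale-up and national implementation will be explored if the program proves effective.

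**The concern.** Hypothesis 3 and the efficacy sentence make a causal claim, but the quantity behind them is a change from baseline in people who were all treated. That change is the sum of at least three parts: the effect of the messages, the background trend in distress, and regression to the mean among people who chose to subscribe. Nothing described for the efficacy analysis separates them.

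The limitation in the Discussion does not alter the hypothesis, the efficacy criterion or the scale-up condition. A reader of the results would be told that the program worked, or did not, on evidence that cannot distinguish these cases.

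**Working it through.** **1. The plan's own figure.** Expected survey completers: 300,000 × (20,000 / 100,000) = 60,000, as stated under Results. The unrounded prior response rate of 21.7% would give 65,100; the article rounds down, which is not an error. No alpha, standard deviation or power value is given, so no power figure can be reproduced.

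**2. Does sample size or multiplicity correction protect against the bias?** Assume two-sided alpha 0.05, Bonferroni over six tests (three scales, two times), and n baseline to follow-up pairs. The critical value is z(1 − 0.05/12) = 2.638.

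- Smallest standardised within-subject change detectable with 80% power at n = 60,000: (2.638 + 0.842) / √60,000 = 0.014. Uncorrected: (1.960 + 0.842) / √60,000 = 0.011.
- Chance that a downward drift d unrelated to treatment is declared a significant reduction: Φ(d√n − 2.638). For d = 0.02 and n = 60,000: Φ(4.899 − 2.638) = 0.99. If only 6,000 pairs were available and d = 0.05: Φ(3.873 − 2.638) = 0.89.

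A large sample makes a small drift significant, and the correction does not prevent this.

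**3. Can the 25% threshold be met with zero effect?** The documents give no means, standard deviations or correlations, so the following are assumptions: r, the baseline to follow-up correlation; k, the subscriber baseline mean divided by the population mean; g, the proportional background decline. With equal variances and linear regression to the population mean, the proportional fall from regression alone is (1 − r)(1 − 1/k). With background decline it becomes

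1 − (1 − g)[1 − (1 − r)(1 − 1/k)].

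| r | k from 1.25 to 2, g = 0 | same k, g = 20% | k giving 25% with g = 0 |
|---|---|---|---|
| 0.5 | 10% to 25% | 28% to 40% | 2.0 |
| 0.6 | 8% to 20% | 26% to 36% | 2.67 |
| 0.7 | 6% to 15% | 25% to 32% | 6.0 |

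Worked case: r = 0.6, k = 1.5, g = 15%. The regression part is 0.4 × (1 − 1/1.5) = 0.133. The total is 1 − 0.85 × 0.867 = 26.3%.

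**4. Can the bias run the other way?** Hypothesis 1 predicts that prevalence will rise. With a 10% background rise (g = −10%) and the same ranges of r and k, the zero-effect change runs from −3% (an increase) to 17.5%. At r = 0.7 and k = 1.25 the no-effect multiplier is 1.10 × (1 − 0.3 × 0.2) = 1.034. A true 25% reduction would then appear as 1 − 0.75 × 1.034, about 22%, and miss the threshold.

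**5. Do the two comparisons in the Discussion supply the missing counterfactual?** The effect sizes reported under Background (d = 0.85 and 0.67) describe "symptom reduction on a standardized self-report when compared to a similar patient group that did not receive text messages", in patients with depression. They are between-group contrasts, whereas Text4Hope yields a within-group change that includes natural course. The Discussion does not say which prior effect sizes it will use, so this applies to those the article reports. The satisfaction comparison is made only among recipients, and people who improve for any reason may report more satisfaction.

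**The case against.** The strongest reply is that the article already discloses the problem. It names the missing control, ties it to hypothesis 3 and gives an ethical reason. It is also a condensed account that offers its models only as examples. All of this is fair, and there is no concealment. Disclosure in the Discussion nevertheless leaves the causal wording of the hypothesis and the efficacy sentence standing, and those are stated, not omitted.

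Four stronger readings are tempting, and the documents do not support them.

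- A reader might infer that the two comparisons are offered as a replacement control. The text claims only that they indicate engagement.
- A reader might infer that calendar time and staggered entry are ignored. Subscription date relative to pandemic phase is a listed secondary interaction, and early- and later-phase prevalence are also compared. These do not identify an effect, but they are in the plan.
- A reader might infer that the bias must flatter the program. Hypothesis 1 predicts rising prevalence, and the Results section calls conditions unpredictable.
- A reader might measure regression to the mean in subscribers above a clinical cut-off. One research question does mention Canadians in distress, but neither the primary outcome nor hypothesis 3 sets a cut-off, so such a figure would not describe the planned analysis.

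**Conclusion.** The concern holds in this form: the article attributes an uncontrolled change from baseline to the intervention and ties scale-up to effectiveness, while its handling of pandemic conditions lies outside the efficacy criterion. The 25% threshold can be reached with no effect, and a real effect can also be hidden.

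The size rests wholly on assumed values of r, k and g. Regression to the mean alone reaches 25% only under strong selection (k of 2 or more when r is at least 0.5); with a background decline of 15% to 20%, much weaker selection is enough. That subscribers join when unusually distressed is an inference from self-subscription, not a stated fact. It cannot be said that hypothesis 3 will be falsely confirmed, only that confirming it would not show efficacy.

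**What to change.** 1. Reword hypothesis 3 and the efficacy sentence under Results as change from baseline at 6 and 12 weeks, without attributing it to the intervention.

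2. Add to the efficacy analysis a calendar-time-adjusted comparison. Subscription is expected to continue over 6 months, and each newcomer is invited to a baseline survey with the first message. New subscribers' baselines therefore overlap in calendar weeks with earlier subscribers' 6- and 12-week surveys. Fit a mixed model to all surveys with time since subscription (0, 6, 12 weeks), calendar week, demographics and a subject effect. State that it removes calendar trend but not regression to the mean, help-seeking selection or attrition: newcomers' baselines are taken when they seek help, and follow-up scores come from those who still respond. A favourable coefficient therefore does not by itself restore causal wording.

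3. State that the comparison with prior effect sizes and the satisfaction correspondence bear on engagement only and are not evidence of specificity.

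The cost is wording and modest extra analysis of data the plan already collects; no one is denied the messages, so the ethical objection to a control group does not apply. The comparison assumes that successive cohorts are comparable given the covariates, and the resulting claim is more conservative.

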### Sample Size Considerations

Based on previous experience using the technology, (ie, >10,000 recipients within 6 months), we expect about 300,000 Canadians to subscribe to the Text4Hope program over the next 6 months. Based on a response rate of 21.7% for our prior Text4Mood survey [27], we anticipate around 20,000 responses to the Text4Hope surveys per 100,000 subscribers.

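### The uncontrolled fall at 6 and 12 weeks is called efficacy, but no planned analysis removes calendar drift from it

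*Protocol article*

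**What the plan says.** Outcome Measures defines the endpoint: "The primary outcome is changed scores at 6 and 12 weeks from baseline on the Perceived Stress, GAD-7, and PHQ-9 scales". Hypothesis 3 words the expected result causally: "The intervention will result in a 25% or greater reduction in perceived stress, anxiety, and depressive symptoms". Results then equates the two: "We will evaluate the efficacy of Text4Hope with the reductions of perceived stress, anxiety, and depression at 6 weeks and 12 weeks". The conventional analysis is exemplified by "within-subject general linear models", "including multiple comparison Type 1 error corrections", and no calendar term is named.

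Calendar time appears in three places.

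- **Results:** infection, death and economic measures at baseline, week 6 and week 12 are called important. Their destination is stated: "Such variables will be included in the machine learning analysis of the project data".
- **Outcome Measures:** one secondary outcome is the interaction of the primary outcomes with subscription date relative to pandemic phase. Another is the change in prevalence from an early to a later phase.
- **Hypotheses:** hypothesis 1 expects prevalence to rise as the pandemic goes on.

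The Discussion admits that the missing control group raises a question of specificity for hypothesis 3. It argues that "it would be unethical to include a control group in the current protocol" and offers comparison with effect sizes from prior work, together with satisfaction responses, as an indicator of engagement.

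On recruitment, "we expect about 300,000 Canadians to subscribe to the Text4Hope program over the next 6 months", and each subscriber is invited to a baseline survey with the first message (Evaluation Methodology and Measurement Plan).

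**The concern.** A change from baseline without a comparator contains whatever happened to everyone over those 6 or 12 weeks. The protocol itself says conditions will move over that interval, yet none of its stated analyses takes that movement out of the number it calls efficacy. The 25% criterion could then be met with inert messages if distress eased generally, or missed with effective messages if distress rose as hypothesis 1 predicts.

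The design offers a partial remedy that the plan does not use. Sign-up is rolling, so in most calendar weeks baseline scores from people who have just joined exist beside 6- or 12-week scores from earlier joiners. The course of the new-joiner baselines estimates the drift, and nobody is denied messages.

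**Working it through.** **1. The plan's own figure.** 300,000 × 20,000/100,000 = 60,000 expected survey completers, as stated. (The unrounded 21.7% gives 65,100; this is rounding and has no bearing here.) The article gives no alpha, SD or 6/12-week response rate. Assumed below: two-sided 0.05; baseline mean 10 and SD 5; pre/post correlation ρ of 0.5 to 0.7 (0.6 in the simulation); follow-up response 10 to 50%; even sign-up over 26 weeks; stable subscriber mix.

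**2. What each planned element does to drift.** Let g(t) be the common level in calendar week t and e the benefit. For a cohort joining in week c, the expected 6-week change is g(c+6) − g(c) − e.

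- *Within-subject model:* estimates that whole sum.
- *Interaction with subscription date:* compares g(c+6) − g(c) between cohorts. If drift is steady, this is equal in all cohorts, the interaction is zero, and the drift stays in the estimate.
- *Early-to-late prevalence:* may describe drift, but is not subtracted from anything.
- *Machine learning:* predicts change scores and is judged by Pearson correlation, which does not alter when a constant is added to every score. No drift-adjusted effect is planned from it.
- *Prior effect sizes and satisfaction:* neither measures g.

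**3. Sample size does not help.** The standard error of a mean change, in SD units, is √(2(1−ρ))/√n. Suppose e = 0 and drift is 0.05 SD. With 6,000 pairs (10% of 60,000) and ρ = 0.5, SE = 1/√6,000 = 0.0129 and 0.05/0.0129 = 3.87, so P(significant) = Φ(3.87 − 1.96) = 0.97. With ρ = 0.7 it is 0.999. With 30,000 pairs, a drift of 0.02 SD is enough for 0.93 to 0.99.

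**4. Size against the 25% criterion.** Simulation of 26 weekly cohorts, linear drift, 30% follow-up; percentages are of the mean baseline over all cohorts:

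| True effect | Drift per 12 weeks | Pre-post, week 6 | Pre-post, week 12 |
|---|---|---|---|
| 0 | -2.5 | -1.27 (-17%) | -2.54 (-34%) |
| 0 | -1 | -0.56 (-6%) | -1.03 (-12%) |
| 0 | 0 | 0.02 (0%) | 0.03 (0%) |
| -2.5 | 0 | -2.55 (-25%) | -2.53 (-25%) |
| -2.5 | +1 | -2.00 (-18%) | -1.58 (-14%) |
| -2.5 | +2.5 | -1.21 (-10%) | -0.01 (0%) |

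The bias equals the drift in points. The 34% exceeds 2.5/10 because the average baseline itself falls to 10 − (2.5/12) × 12.5 = 7.4.

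**5. Can the planned data estimate the drift?** 60,000/26 = 2,308 baselines per week. At 6 weeks, 20 cohorts have follow-up in a week when new baselines still arrive; at 12 weeks, 14 do.

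For the drift-corrected change, averaged over cohorts:

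- *Week 6:* the 20 baseline differences telescope to the last six weeks minus the first six, with variance 12/(20² × 2,308), SE 0.0036 SD. The change term at 10% follow-up and ρ = 0.5 has SE 1/√4,615 = 0.0147. Together: √(0.0036² + 0.0147²) = 0.015 SD, about 0.08 points at SD 5.
- *Week 12:* 24/(14² × 2,308) gives 0.0073; 1/√3,231 = 0.0176; together 0.019 SD, about 0.10 points.

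These sums ignore the covariance between the two terms, which is negative and would lower them slightly.

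**6. Why not the raw same-week contrast?** Follow-up scores minus same-week new baselines is about as precise (0.0154 and 0.0185 SD at 10% follow-up). With response unrelated to score, it recovered the truth in the simulation: -0.09 to +0.11 for a zero effect, -2.38 to -2.57 for -2.5. But it compares selected follow-up responders with all new joiners. If a fraction f responds and responders start 1 point lower than non-responders (assumed), the false benefit is (1−f) × 1 = 0.9, 0.8 or 0.6 points at f = 0.1, 0.2 or 0.4. Within-person change compares the same people, so a stable difference of this kind cancels.

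**The case against.** The best defence is that the authors see the problem and say so: the Discussion raises specificity for hypothesis 3, and two secondary outcomes involve calendar time. That stands against some stronger readings that a reader might infer.

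- *Drift is handled only in machine learning.* Not so; Outcome Measures lists the two secondary outcomes. What stands is that neither nets drift out of the efficacy estimate.
- *The authors wave the missing control away as unavoidable.* That word in the Discussion concerns the absent data from before self-isolation. On controls the argument is ethical, and the limitation is conceded.
- *The plan inflates the benefit.* The direction is unknown. Under hypothesis 1, drift would hide a benefit.
- *The machine learning models could never separate drift from effect.* Too strong. With staggered entry, covariate changes differ between cohorts, so a change-score model could adjust in part. The stated aim, though, is prediction.
- *Scale-up rests on this estimate.* The Discussion makes scale-up conditional on effectiveness but names no threshold, and Results lists several evaluation dimensions.

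A second defence is that any comparator built from later joiners brings assumptions of its own. This also stands. It is why the raw same-week contrast should not become the key estimate.

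**Conclusion.** The point holds in this form: hypothesis 3 is to be judged on a quantity that mixes the messages' effect with calendar drift, and no stated analysis separates them. The bias equals the drift, runs either way and is untouched by sample size. Under the assumed mean of 10, a drift of 2.5 points over 12 weeks is as large as the whole 25% target. The actual drift is unknown, and the point figures rest on the assumed mean, SD, correlation, follow-up rates, even sign-up and linear drift. That the pre-post estimate contains the drift needs none of these.

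The documents do not support saying that the messages will be falsely credited, or that the authors overlooked the missing control. What is unsupported is the step from change to efficacy, given that the offered substitute speaks to engagement.

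**What to change.** 1. In Hypotheses and Results, call the 6- and 12-week fall a change from baseline, not efficacy.
2. Prespecify a supporting drift-corrected analysis: within-person change at 6 and 12 weeks minus the change in new-subscriber baseline means between the same calendar weeks, adjusted for the demographics already collected. A same-week contrast restricted or weighted for follow-up response is an alternative.
3. State its limits. It assumes later joiners resemble earlier ones after adjustment. It loses precision if sign-up is front-loaded. It leaves regression to the mean after self-referral and any residual selective follow-up.

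The cost is a change of wording and one further model. No new data are needed and no subscriber goes without messages. The within-person form needs surveys linked across waves, as the planned within-subject models already do.
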